## Abstract

**Background:**

Antibiotic-resistant strains of pathogenic bacteria are increasingly prevalent in hospitals and the community. Acute exacerbations of COPD (AE-COPD) often result in administration of antibiotics although more than half of exacerbations are associated with detection of respiratory viruses and potentially pathogenic bacteria can only be detected in 20-30% of cases. There is a paucity of placebo-controlled clinical trials and up to today no single study has been powered sufficiently to prove the efficacy of antibiotic treatment in AE-COPD. Most studies so far did not include current standards of care comprising administration of systemic corticosteroids.

**Methods/Design:**

A total of 980 patients with moderate acute exacerbations will be included in 22 German centers (hospitals and private practices). Patients will receive a standardized treatment for exacerbation including systemic corticosteroids, inhaled bronchodilators and supplementary oxygen if needed and will be randomized to additional treatment with placebo or antibiotic (oral sultamicillin) for five days.

The primary endpoint is clinical failure defined by need for additional antibiotic treatment until day 30. Secondary endpoints will assure that management of AE-COPD without antibiotics does not result either in increased occurrence of relapse, new exacerbations, prolonged recovery, or unwanted long-term consequences.

**Discussion:**

ABACOPD will be the first sufficiently powered double-blind placebo-controlled study in the field to systematically assess the question whether antibiotics, known to increase antibiotic resistance, are really needed in a well-defined patient cohort receiving state-of-the art treatment in all other aspects.

**Trial registration number:**

ClinicalTrials.gov: NCT01892488.

## Background

Antibiotic resistance is increasing in hospitals as well as in the community. It has been shown that antibiotic prescriptions without a clear indication contribute significantly to this increase [1]. Acute exacerbations of COPD (AE-COPD) represent a frequent clinical situation in which administration of antibiotics is considered. In 2010 nearly 700.000 hospital discharges for COPD in the U.S. [2] have been registered. A retrospective cohort study identified that antibiotics were prescribed in 85% of 69 820 patients admitted for acute exacerbations of COPD to 360 hospitals throughout the United States [3]. This is impressive as evidence of efficacy of antibiotic treatment of AE-COPD is scarce. It is estimated that about 70% of exacerbations are infectious in origin [4]. However, only 20-30% are associated with detection of bacteria by sputum culture [4]. Importantly, detection of pathogens by culture is not per se a proof of infection. Particularly in COPD patients growth of bacteria in sputum cultures can also result from colonization of the airways [5]. Up to now colonization is not considered as a clear indication for antibiotic treatment. In addition, others and we have shown that respiratory viruses are detected in more than 50% of exacerbations and also have to be considered as major infectious triggers [6, 7]. In viral infections antibiotic therapy is not expected to be effective [8]. Moreover antibiotic treatment is associated with increased morbidity, mainly reflected by gastro-intestinal complications such as diarrhoea, often caused by C. difficile [9].

A recent Cochrane review assessed the effects of antibiotics in the management of acute COPD exacerbations on treatment failure as observed between seven days and one month after treatment initiation (primary outcome) and on other patient-important outcomes (mortality, adverse events, length of hospital stay) [10]. In this most recent systematic review using GRADE methodology [11] 16 trials with 2068 participants were included. Outpatients were considered to have mild to moderate exacerbations. Only the most recent trial showed a benefit of antibiotic treatment and drove the results towards beneficial effects of antibiotics [12]. When the meta-analysis was restricted to currently available drugs however, there was no significant benefit but just a trend in favour of antibiotics (RR 0.80; 95% CI 0.63 to 1.01; I2 = 33%) [10]. However, evidence of high quality showed that antibiotics significantly reduced the risk of treatment failure in inpatients with severe exacerbations (ICU not included) (RR 0.77; 95% CI 0.65 to 0.91; I2 = 47%) regardless of whether restricted to current drugs or not. There still is only one trial with 93 patients admitted to the ICU, which was also analysed in this review [13]. This trial showed a large and statistically significant effect on treatment failure (RR 0.19; 95% CI 0.08 to 0.45; high-quality evidence) [10]. In studies addressing mortality evidence of low-quality from four trials in inpatients showed virtuality no effect of antibiotics on mortality (Peto OR 1.02; 95% CI 0.37 to 2.79) [10]. Length of hospital stay (in days) was similar in the antibiotics and placebo groups except for the ICU study. The overall incidence of adverse events was higher in the antibiotics groups (Peto OR 1.53; 95% CI 1.03 to 2.27). Patients treated with antibiotics experienced more diarrhoea based on three trials (Peto OR 2.62; 95% CI 1.11 to 6.17; high-quality evidence) [10]. The authors concluded on the basis of these findings that for outpatients and inpatients the results were inconsistent. The risk for treatment failure was significantly reduced in both inpatients and outpatients when all trials (1957 to 2012) were included but not when the analysis for outpatients was restricted to currently used antibiotics. Also, antibiotics had no statistically significant effect on mortality and length of hospital stay in inpatients and almost no data on patient-reported outcomes exist [10]. The appraisal of the results of this systematic review is largely impaired by the fact that there was no pre-defined standard treatment of AE-COPD including corticosteroids, even not in the most recent trials. Therefore it is impossible to judge the benefit of antibiotic treatment in addition to standard treatment of AE-COPD.

It is remarkable that on this brittle basis, antibiotic treatment for AE-COPD is recommended for patients with severe exacerbations or severe underlying COPD [8]. Moreover, most AE-COPD are mild to moderate and not severe and it seems difficult to extrapolate the findings from one positive ICU study to the less severe situations.

In conclusion there still is no clear recommendation for antibiotic treatment for these patients. These facts underline that a randomized, placebo-controlled trial on antibiotics for mild to moderate AE-COPD is warranted [8]. In light of the fact that respiratory viruses are detected in 50% of exacerbations a major task is the reduction of unnecessary antibiotic treatment in patients with mild to moderate COPD exacerbations to stop the threatening increase in AB resistance [8]. It has been convincingly shown that prudent reduction of antibiotic use results in a decrease of bacterial resistance without an increase in complications [14]. Taken this important aspect into account it seems that the risk-benefit ratio of antibiotic treatment for mild to moderate AE-COPD is negative and should therefore be discouraged. The most recent study [15] showed that it is safe to treat AE-COPD patients with all grades of disease severity (GOLD 1 to 4) with placebo if standardized treatment is provided. All studies performed so far were designed to prove efficacy of antibiotics in AE-COPD [8].

Against this background we have designed a randomized double blind placebo-controlled study to demonstrate that antibiotics are not needed in moderate acute exacerbations of COPD – The ABACOPD Study. ABACOPD is the first study designed to show non-inferiority of placebo in AE-COPD proving that antibiotics are not needed. This might have important impact to individual patients as well as to society. It has been shown in several trials that adverse events are more frequent in patients treated with antibiotics than in patients on placebo [16]. Hence the individual patient might benefit from reduced adverse events associated with antibiotic treatment if antibiotics are no longer prescribed for this indication. In addition the individual patient might also benefit from decreased selection of antibiotic resistant strains by reduction of antibiotic consumption. Society will clearly benefit if unnecessary antibiotic prescriptions will be reduced. This has been convincingly shown in other settings [14]. At last there is a potential economic impact. Antibiotic therapy can be costly and it has been shown that reduction in antibiotic use significantly reduces costs [17].

## Methods

### Objective

The ultimate goal is to reduce unnecessary antibiotic prescriptions, which drive the development of antibiotic resistance in the community. The primary objective of ABACOPD is to demonstrate in a sufficiently sized clinical study that there is no relevant increase in the “failure-rate” for patients with acute moderate exacerbations of COPD (AE-COPD) treated with placebo instead of antibiotic treatment both on top of standard of care. A patient is classified as treatment failure if additional antibiotic therapy is required during the initial treatment period or until the test of cure visit (TOC at day 30, primary endpoint). Secondary objectives are to demonstrate that patients on placebo do not experience more frequent relapse or show prolonged symptoms. A patient is classified as relapse if new antibiotic therapy for AE-COPD is required within the first six months after TOC. Clinical cure rates at end of treatment (EOT) and TOC will inform about duration of symptoms and speed of recovery.

### Intervention

Each patient will receive inhaled short-acting bronchodilators, systemic corticosteroids (prednisolone 40 mg/d p.o. for 7–10 days) and oxygen in case of hypoxemia in a standardized fashion. The pre-existing COPD medication will be continued as indicated. All patients in the study will receive, per randomized allocation, treatment with either antibiotic therapy or placebo. Those randomized to antibiotic therapy will receive 750 mg sultamicillin (two 375 mg capsules) twice a day (BID) for 5 days. An Aminopenicillin plus betalactamase inhibitor is the recommended antibiotic treatment for moderate AE-COPD in Germany [18]. The treatment duration of 5 days is chosen because the latest interventional trial in lower respiratory tract infections showed for patients with AE-COPD that 5 days of treatment is safe and effective and that even shorter duration can be used if procalcitonin guidance is employed [19]. Those patients randomized to the placebo will receive two placebo capsules twice a day (BID) for 5 days. The duration of treatment with study medications will be 5 days.

### Key inclusion criteria

Patients will be enrolled into the study when diagnosed with moderate acute exacerbation of COPD according to the definition of the Global initiative for chronic Obstructive Lung Disease (GOLD) without respiratory failure or need for intermediate or intensive care if they fulfill the following criteria:Male and non-pregnant female adults, older than 40 years of age, diagnosed with COPD stages I-IV as defined by GOLDDoctor’s diagnosis of acute (onset < 7 days) moderate exacerbation of COPD (definition see 3.2), necessitating the administration of systemic corticosteroidsProcalcitonin level < 0.25 ng/mL (to rule out community acquired pneumonia or lower respiratory tract infection with a clear indication for antibiotic treatment)Smoking history of 10 Pack Years or more

### Key exclusion criteria

Severe exacerbation defined by need for ventilatory support indicated by PaCO2 > 45 mmHg and/or pH < 7.35, mental confusion, or unstable comorbiditiyPneumonia (proven by chest x-ray performed in suspected cases)Fever (>38.5°C)Known impaired hepatic or renal functionActive or suspected tuberculosis infection of the respiratory tractAcute exacerbation of asthmaSuspected or known hypersensitivity to, or suspected serious adverse reaction to SultamicillinImmunosuppression or Immunosuppressive therapyAntibiotic use within 30 days prior to randomizationAn antibiotic is clearly indicated for treatment of a known infectionKnown MRSA colonization or infectionPatients with known bronchiectasis

### Outcomes

#### Primary efficacy endpoint

A test of cure (TOC)-visit will be performed at day 30 after start of the treatment phase. A patient is classified as a treatment failure if additional antibiotic therapy is required during treatment period or until the TOC-visit. For each treatment arm a failure rate will be computed.

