### Key criteria for safety are

Adverse eventsSerious adverse eventsIncidence of complications (Need for intensive care unit treatment, need for ventilatory support)Vital status

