### Statistical analysis

#### Efficacy/test accuracy

A patient is classified as a treatment failure if additional antibiotic therapy is required during treatment period or until the test of cure visit (TOC at day 30, primary endpoint).

The primary analysis will be stratified for centre. A two-sided 95%-confidence interval will be computed for the difference in failure rates for placebo minus experimental treatment group. The null-hypothesis of relevant inferiority of the placebo treatment will be rejected in favor of the alternative that antibiotic treatment is not required in this patient population, if the upper bound of the confidence interval does not exceed 10%, which is standard for the comparison of antibiotic treatments. The primary analysis will be conducted on the ITT-population including all randomized patients that have taken experimental drug or placebo at least once. A conservative rule will count missing values in the placebo-group with treatment failure, and as success in the active treatment group.

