### Sample size calculation

A limited number of studies have compared antibiotic treatment to placebo in patients with AE-COPD. Jorgensen et al. [20] found in 1992 a 63% success rate with placebo as compared to 64% with Amoxicillin after 7 days of treatment of uncomplicated exacerbations of chronic bronchitis. In contrast Anthonisen et al. [21] found in 1987 a 55% success rate with placebo and a 68% response rate with antibiotic treatment for 10 days. Daniels et al. [15] observed in 2010 a clinical success in the first study using a standardized treatment including systemic corticosteroids in 61% of patients from the doxycycline group and 53% from the placebo group. In all these studies background standard of care has not been optimized and it is assumed that this is the reason for observed differences in small studies. It is thus assumed that the response rate in the study population will be in the order of 65%. With a one-sided type 1 error of 2.5% 479 patients per group have to be recruited to reject the null-hypothesis of relevant inferiority of placebo treatment with 90% power and a non-inferiority margin of 10%. (Sample-size calculation has been performed with nQuery-Advisor 7.0).

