The sample size of this trial is assumed to be sufficient to determine changes in relapse rates, time to relapse, clinical cure rates at EOT and TOC and to assess long-term consequences of sparing anti-biotic treatment.

This is a randomized and double-blind clinical trial with placebo matching tablets for active treatment. Block-randomization will be used. Randomization will be stratified for centre. All randomized patients that have received study medication at least once will be included into the primary intention-to-treat (ITT)-analysis. This is a non-inferiority trial and usually a per-protocol analysis would be used as primary analysis. However, the impact of potential missing values could be anti-conservative in the per-protocol analysis when demonstrating non-inferiority to placebo as well (pts with no improvement to placebo drop) and the ITT population is used here with a strategy that should maximize differences between treatment groups in case of uncertainty about outcome, because irrelevance of differences between treatment strategies is the objective to be demonstrated. In this complex situation missing values will be counted as failure in the placebo-group and as a success for patients in the antibiotics group. It is obvious that all attempts have to be undertaken to follow all patients to the end of the study.

In conclusion we believe that ABACOPD will be the first sufficiently powered double-blind placebo-controlled study in the field to systematically assess the question whether antibiotics, known to increase antibiotic resistance, are really needed in a well-defined patient cohort receiving state-of-the art treatment in all other aspects.

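### The primary failure definition does not provide for death before day 30: read literally it is a non-failure in both arms, read as missing it is scored by arm

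*Protocol article*

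**What the plan says.** The protocol article gives the same one-component definition in the abstract, under Objective, under Primary efficacy endpoint and under Efficacy/test accuracy. The abstract puts it as "The primary endpoint is clinical failure defined by need for additional antibiotic treatment until day 30", and Primary efficacy endpoint as "A patient is classified as a treatment failure if additional antibiotic therapy is required during treatment period or until the TOC-visit".

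The list of key safety criteria contains vital status and complications, the latter specified as "Need for intensive care unit treatment, need for ventilatory support". No sentence turns any of these into a primary failure.

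For missing outcomes, Efficacy/test accuracy states: "A conservative rule will count missing values in the placebo-group with treatment failure, and as success in the active treatment group". The Discussion repeats it: "In this complex situation missing values will be counted as failure in the placebo-group and as a success for patients in the antibiotics group". The reason given there is that the analysis should make the arms look as different as possible where the outcome is in doubt. Death is not mentioned in either place.

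Non-inferiority of placebo is concluded "if the upper bound of the confidence interval does not exceed 10" percent, for the failure rate on placebo minus that on antibiotic.

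**The concern.** The trial asks whether withholding antibiotics does relevant harm. A patient who dies before the TOC visit without having received a further antibiotic has the worst possible result, and the stated rules do not give that result a sound place in the primary comparison.

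- **Literal definition.** No additional antibiotic was given, so the patient is not a failure, in either arm. An excess of such deaths on placebo would then not enter the primary difference at all. In a non-inferiority trial that error favours the claim.
- **Death as a missing value.** There is no TOC visit, so the missing-data rule applies: failure on placebo, success on antibiotic. The same known event is scored by allocation and not by outcome. The error runs against the claim and costs power.

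On both readings a death on antibiotic without a new antibiotic is a success. Only the placebo death changes sides.

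**Working it through.** **Inputs from the article.** Response rate: "the response rate in the study population will be in the order of 65" percent, taken as equal in both arms, so failure 35%. Margin 10 points, one-sided alpha 2.5%, power 90%, 479 per group (Sample size calculation). 980 patients allocated (Study populations), that is 490 per arm if allocation is 1:1, which is assumed here.

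**Input not in the article.** d is the share of an arm that dies by day 30 without a new antibiotic and would otherwise be a non-failure. The article gives no such rate, so a range is shown.

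**Step 1: the plan's own figure.** n = 2 × 0.65 × 0.35 × (1.960 + 1.282)² / 0.10² = 479 per group after rounding up. It reproduces. Power at 479 per group is 90.05%.

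**Step 2: formula.** Let pP and pA be the failure rates as scored on placebo and antibiotic.

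SE = √[pP(1 − pP)/479 + pA(1 − pA)/479]

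Power = Φ[(0.10 − (pP − pA))/SE − 1.96]

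**Step 3: equal true mortality d in both arms.**

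- Literal reading: pP = pA = 0.35.
- Missing reading: pP = 0.35 + d, pA = 0.35.
- Failure in both arms: pP = pA = 0.35 + d.

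Example for the missing reading at d = 1%: SE = √[(0.36 × 0.64 + 0.35 × 0.65)/479] = 0.0309, and Φ(0.09/0.0309 − 1.96) = 82.9%.

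| d | Literal | Missing | Failure in both arms | n per arm for 90% if failure in both |
|---|---|---|---|---|
| 0.5% | 90.1% | 86.8% | 89.9% | 482 |
| 1% | 90.1% | 82.9% | 89.7% | 485 |
| 2% | 90.1% | 73.2% | 89.4% | 490 |

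With the SE held at a constant 0.0309, the 2% entry in the missing column becomes about 74%.

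**Step 4: unequal mortality (illustrative), probability of concluding non-inferiority.**

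| Deaths, placebo vs antibiotic | Difference if deaths are failures in both arms | Literal | Missing | Failure in both arms |
|---|---|---|---|---|
| 3% vs 1% | +2 points | 90.1% (difference scored 0) | 61.5% (scored +3) | 72.7% |
| 1% vs 3% | −2 points | 90.1% (difference scored 0) | 82.9% (scored +1) | 97.0% |

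The literal reading ignores the imbalance whichever way it runs. The missing reading responds only to placebo deaths, so it overstates the difference by exactly the antibiotic-arm mortality: 3 − 2 = 1 point in the first row, 1 − (−2) = 3 points in the second.

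**The case against.** The case on the other side has several parts.

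- **This is a condensed article.** Whether a death counts as observed or missing is often settled in a full protocol or analysis plan, and neither is shown. That is fair as to the silence on deaths. It does not answer the whole point, because the one-component definition and the arm-dependent rule are both stated here, and neither suits a known death.
- **The affected group is probably small.** Enrolment is limited to moderate exacerbations without respiratory failure or need for intermediate or intensive care, and pneumonia is excluded. The Background notes that antibiotics are recommended in severe exacerbations, so many deteriorating patients would receive one and already count as failures. This stands. The rates used above are assumptions.
- **The events are not lost.** Vital status, intensive care, ventilation and serious adverse events are safety criteria, and adverse and serious adverse events are compared descriptively between arms. This stands too, but none of it enters the non-inferiority criterion.

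A reader might also infer more than the text supports:

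- *That a placebo death is both a success and a failure.* The two readings exclude each other, and the article adopts neither expressly.
- *That patients in intensive care or on ventilation pass through the missing-data rule.* Their antibiotic status is observed. By the definition they are non-failures in both arms unless a new antibiotic is required, so the power losses above apply to deaths only.
- *That the missing-data rule could hide harm on placebo.* It scores against placebo. The anti-conservative risk belongs to the literal reading alone.
- *That intensive care and ventilation must join the primary endpoint.* That is a debatable design choice. The stated objective concerns the need for further antibiotics.

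**Conclusion.** The point holds in this form: the primary definition counts only additional antibiotics to day 30, and it leaves a death before TOC without a new antibiotic either as a non-failure in both arms or, if treated as missing, as a failure on placebo and a success on antibiotic. Neither coding is sound for a claim that treatment can be withheld. The first is anti-conservative if deaths are more frequent on placebo. The second is conservative, and its cost is arm-dependent coding of a known event and power of about 87%, 83% and 73 to 74% at assumed equal mortality of 0.5%, 1% and 2%.

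These sizes rest on assumed mortality, on a 35% failure rate otherwise and on 479 per arm. The sample size itself is correct. The real effect is probably small, but the stated rule can be put right at very little cost.

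**What to change.** 1. In the endpoint definition, count as failure additional antibiotic therapy **or death from any cause** before the TOC visit, scored identically in both arms.
2. State that the arm-dependent missing-data rule applies only to patients whose antibiotic and vital status at day 30 is truly unknown. This fits the rationale in the Discussion, since a known death is not a case of doubt about the outcome.
3. Add a sensitivity analysis that also counts intensive care treatment or ventilatory support without a new antibiotic as failure in both arms, using the safety data already planned.
4. Show the antibiotic-only component alongside the primary result.

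The cost is two sentences and a few extra events in the primary endpoint: at 479 per arm, about 5 at 1% mortality (0.01 × 479) and about 10 at 2%. Power falls from 90.1% to 89.7% and 89.4% respectively. Keeping 90% would need 485 or 490 per arm, which the 490 per arm allocated (980/2, assuming 1:1) would cover if nearly all are analysed. At the 960 the article expects to analyse, power stays just under 90%. No new data collection is needed.
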